# A single-blind, randomized, crossover study on the efficacy of icatibant for sweating-induced dermal pain (icatibant for sweating-induced dermal pain)

**DOI:** 10.1097/MD.0000000000033971

**Published:** 2023-06-09

**Keywords:** bradykinin, bradykinin B2 receptor, dermal pain, icatibant, sweating

## Abstract

**Methods/design::**

A multicenter, exploratory, crossover, single-blinded, placebo-controlled randomized, comparative study will be conducted to evaluate the efficacy of subcutaneous icatibant injection (30 mg) in treating sweating-induced dermal pain. Ten patients will be enrolled and assigned randomly in a 1:1 ratio to either the icatibant-placebo or placebo-icatibant groups. The primary endpoint is the change in the visual analog scale scores for dermal pain induced by thermal load before and after treatment with icatibant or placebo. Secondary endpoints include changes in the duration of dermal pain, blood and plasma histamine levels, serum angiotensin-converting enzyme levels, and histological evaluation of skin tissue samples at the site of dermal pain.

**Discussion::**

The effectiveness of icatibant against sweating-induced dermal pain would provide clear evidence for the involvement of the bradykinin-bradykinin B2 receptor pathway in the pathogenesis of this condition. This finding may contribute to a better understanding of the underlying mechanisms of dermal pain associated with sweating stimuli and has the potential to improve patients’ quality of life by suggesting potential treatment options, specifically, using drugs that inhibit bradykinin or suppress its production.

## 1. Introduction

In a certain population of individuals, the exposure to sweating stimuli such as bathing, exercise, or mental stress, leads to severe dermal pain.^[1–3]^ The sweating-induced dermal pain may occur alone or more frequently be accompanied by transient eruptions and/or generalized hypohidrosis. When accompanied by such symptoms, the condition can also be referred to as cholinergic urticaria^[2]^ or acquired idiopathic generalized anhidrosis.^[3,4]^ Such dermal pain predominantly affects young males in their teens and twenties^[1]^ and manifests immediately upon exposure to sweating stimuli, lasting typically for 5 to 10 minutes at a maximum visual analog scale (VAS) level of 100 mm.^[1]^ Although short lived, the pain is severe and significantly disrupts patients daily lives, resulting in absenteeism or withdrawal from school or work.^[1]^ Consequently, there is a substantial unmet need to understand the underlying mechanisms and develop effective treatments.

Despite numerous attempts to treat sweating-induced dermal pain, no standard treatment has been established. Common nonsteroidal anti-inflammatory and analgesic drugs demonstrate little effect. As the condition frequently presents with transient eruptions and/or generalized hypohidrosis, antihistamines and systemic corticosteroids have been tested based on their effectiveness against cholinergic urticaria and acquired idiopathic generalized anhidrosis.^[1,3]^ However, these treatments fail to fully alleviate pain triggered by such stimuli.^[1,5,6]^ The use of psychotropic drugs and neuropathic pain medications has also been explored, but their efficacy varies among patients.^[1,5,6]^ The absence of a suitable animal model for sweating-induced dermal pain complicates the evaluation of therapeutic agents.

The precise pathomechanisms underlying sweating-induced dermal pain remain elusive. Short duration of the pain following sweating stimuli suggests the involvement of endogenous pain-producing substances with short lifetimes, such as histamine and bradykinin in the pathogenesis of sweating-induced dermal pain. High levels of histamine in sweat and elevated plasma histamine levels after thermal sweating in patients with dermal pain compared to healthy subjects^[1]^ support the potential involvement of histamine. However, antihistamines alone do not provide sufficient analgesia. Alternatively, bradykinin may serve as a mediator, inducing dermal pain triggered by sweating stimuli. Kininogen and kallikrein, which are involved in bradykinin production, are reportedly present in sweat glands.^[7]^ Additional study revealed that eccrine sweat gland stimulation by thermal load activated the bradykinin-forming enzyme in the sweat and the formation of bradykinin in the skin.^[8]^ The bradykinin-forming enzyme is shown to be tissue kallikrein, and contribute to generate Lys-bradykinin which acts on bradykinin B2 receptor.^[9,10]^ Localization of kallikrein is detected in luminal ductal cells and in the peripheral rim of secretory coil segments.^[9]^ The stimulation of bradykinin B2 receptor is reported not to be associated with thermally- and pilocarpine-induced sweating itself^[11]^; however, human sweat glands respond to bradykinin stimulation to increase cyclic AMP for flexible control of sweat gland function.^[12]^ Although the role of bradykinin-forming activity detected in sweat glands remains unclear, these suggest that increased bradykinin production in the skin during sweating stimulation could contribute to dermal pain.

This study aims to evaluate the analgesic effect of icatibant, a bradykinin B2 receptor antagonist, on patients experiencing sweating-induced dermal pain and to demonstrate a role of bradykinin in the pathomechanism of dermal pain. Its results are expected to contribute to the development of novel treatments for sweating-induced dermal pain targeting bradykinin and the kallikrein-kinin pathway.

## 2. Methods/design

### 2.1. Study design

This is a multicenter, exploratory, crossover, single-blind, placebo-controlled, and randomized comparative study.

### 2.2. Study setting

Study participants include patients with sweating-induced dermal pain who visit Hiroshima University Hospital directly or are referred to Hiroshima University Hospital by collaborating institutions (Kawasaki Medical School Hospital, Kobe University Hospital, and Nagasaki University Hospital) to seek new treatment options. After obtaining consent from study participants at Hiroshima University Hospital, eligibility will be confirmed based on the inclusion and exclusion criteria. Upon enrollment, participants will be assigned to 1 of 2 groups (Icatibant-placebo group [Group A] or Placebo-icatibant group [Group B]). Treatment drugs will be administered in a single-blinded crossover manner, and dermal pain induced by thermal load will be evaluated before and after administration. To explore related mediators, blood and plasma histamine levels and plasma angiotensin-converting enzyme (ACE) levels will also be measured before and after thermal load.

### 2.3. Inclusion criteria

Male and female subjects aged ≥ 18 years and ≤ 50 years at the time of obtaining consent.Patients with severe dermal pain induced by thermal sweating stimuli (e.g., bathing), regardless of the presence or absence of cholinergic urticaria and hypohidrosis.Patients who have had symptoms of dermal pain for more than 3 months.Patients with a dermal pain degree ≥ VAS 60 mm in their daily life during the 2 weeks before obtaining consent.Patients who have not changed drugs* that may alleviate symptoms during the 2 weeks before obtaining consent and have no plans to change drugs until the end of this study (including injections, oral medications, and topical medications). The asterisk refers to antihistamines, H2 receptor antagonists, leukotriene receptor antagonists, antipyretic analgesics, narcotics, antipsychotics, and drugs acting on the central and peripheral nervous systems.Patients whose consent for participation in this study can be obtained in writing.

### 2.4. Exclusion criteria

Patients with other causes for dermal pain.Patients with atopic dermatitis, Sjögren syndrome, hypothyroidism, Fabry disease, autonomic nervous system disorders, or drug-induced anhidrosis. To exclude these diseases, SS-A antibodies, SS-B antibodies, FT3, FT4, and TSH will be measured, and subjects with abnormal values will be excluded. In addition, α-galactosidase activity will be measured in patients who experience pain in their hands and feet, not related to temperature elevation, and hypohidrosis that appeared before school age. Genetic testing of α-galactosidase may need to be performed in women. Patients with these abnormalities would be excluded from the study.Patients with a history of allergy to icatibant.Patients who are pregnant or breastfeeding.

### 2.5. Randomization and allocation concealment

The study procedures and schedule are shown in Figure 1 and Table 1, respectively. Allocation of study participants to each treatment group will be performed through a central registry. According to a predesigned computer-generated random assignment table, participants will be assigned in a 1:1 ratio to either Icatibant-placebo group (Group A) or Placebo-icatibant group (Group B).

**Figure 1. F1:**
[figure not shown]
Flowchart of the study design.

**Table 1 F2:**
[figure not shown]
Intervention and assessment schedule.

### 2.6. Interventions

Icatibant (30 mg) and placebo (saline, 3 mL) will be subcutaneously injected in a defined order in a crossover manner. Dermal pain induced by thermal load will be assessed before and after administration of both drugs. For blinding, study participants wear an eye mask when receiving the drugs. The investigator will ensure that the study participant has properly donned the eye mask before preparing the drugs and giving them to the participants. After the used syringes are discarded, the participant will be allowed to remove the eye mask. The study will be conducted over 3 consecutive days under hospitalization.

#### 2.6.1. [Day 1].

After collecting patients’ background data, both lower legs will be subjected to thermal load by placing them in warm water (~43°C) for 30 minutes to induce dermal pain.^[13]^ Scheduled examinations and blood sampling will be performed before and after thermal loading. The examinations include VAS for pain, distribution and duration of dermal pain, VAS for itching, and presence or absence of eruption. If unbearable dermal pain occurs during heating, the thermal load will be discontinued, and examinations and blood sampling will be performed. Icatibant (30 mg) or placebo (saline, 3mL) will be subcutaneously injected at least 90 minutes after the first thermal load or 30 minutes after the skin symptoms resolved, whichever occurs later. The second thermal load starts 45 ± 15 min after the drug administration, and the second scheduled examinations and blood sampling will be performed before and after the second thermal load.

#### 2.6.2. [Day 2].

The same procedure as on Day 1 will be followed to administer the drug and conduct the (3rd and 4th) thermal load before and after drug administration. The placebo (saline) will be subcutaneously injected into patients who receive icatibant on Day 1, while icatibant to those who receive placebo on Day 1. A washout period of ≥ 9 h will be allowed between drug administration on Day 1 and 2. The period was established as 5 times the half-life (T1/2 1.7 hours) of icatibant^[14]^ or longer.

#### 2.6.3. [Day 3].

Subjects will be checked for adverse events.

### 2.7. Outcomes

#### 2.7.1. Primary endpoint.

The primary endpoint is the change in the VAS score for thermally-induced dermal pain before and after treatment with icatibant or placebo.

#### 2.7.2. Secondary endpoints.

Changes in the duration of dermal pain induced by thermal load before and after administration of icatibant or placebo.Blood samples will be collected before and after treatment with icatibant or placebo to measure blood and plasma histamine, and serum ACE levels.In patients who consent to a skin biopsy, a skin tissue sample will be obtained to histologically evaluate the pathomechanism of dermal pain. In some patients, a prior skin biopsy may have been performed at the site of dermal pain beforehand in the past clinical practice. If the conditions for obtaining skin samples are consistent with those in this study, the previous specimens would be evaluated to avoid performing another biopsy with patients physical burden.

#### 2.7.3. Adverse events.

Safety concerns in this study are assumed to be associated with the administration of icatibant and the induction of dermal pain by thermal stimuli. Safety will be assessed by monitoring adverse events, physical findings, and changes in vital signs. If an adverse event is clinically suspected, physicians will conduct a thorough examination and safety evaluation.

### 2.8. Statistical methods

#### 2.8.1. Sample size.

Target number of patients is 5 patients in the icatibant-placebo group (Group A), and 5 patients in the placebo-icatibant group (Group B). Considering the minimum number of patients to achieve the study objectives and the rarity of sweating-induced dermal pain, total 10 eligible patients will be enrolled and evaluated in this proof-of-concept study.

#### 2.8.2. Target population for analysis.

The population to be analyzed is defined as follows.

Full analysis set (FAS): The FAS will comprise all study subjects who underwent randomization, excluding the following study subjects: cases that do not meet the eligibility criteria (e.g., diagnosed with another disease, violating objectively determinable inclusion or exclusion criteria), cases that have never received any study treatment after randomization, and cases with no measurements made after randomization.Per protocol set (PPS): The PPS consisted of the FAS population, excluding the following study subjects: cases with unavailable measurements of the primary endpoint and cases with serious protocol violations (e.g., misassignment, failure to meet eligibility, use of prohibited medications, and noncompliance with medications).

#### 2.8.3. Analysis of the primary endpoint.

The primary endpoint of the study is the change in the VAS scores for dermal pain induced by thermal load before and after treatment with icatibant or placebo. The FAS will be used as the analysis population to compare the changes in VAS scores between the 2 treatments at a significance of *P* < .05 (2-tailed). Paired t-tests will be performed to determine the significance of differences.

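### The primary paired t-test has no period term, so a Day 1 to Day 2 difference in the before-to-after VAS change costs power, and biases the estimate if the analysed sequences are unequal

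*Protocol article*

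**What the plan says.** Section 2.5 randomises patients 1:1 to icatibant-placebo (Group A) or placebo-icatibant (Group B). Section 2.8.1 plans 5 patients in each. Sections 2.6.1 and 2.6.2 place the two treatments on Days 1 and 2. Each day has one thermal load before the injection and one after it; on Day 2 the plan is to "conduct the (3rd and 4th) thermal load before and after drug administration".

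The primary endpoint (2.7.1) is a change score: "The primary endpoint is the change in the VAS score for thermally-induced dermal pain before and after treatment with icatibant or placebo". Section 2.8.3 compares these changes between treatments in the full analysis set (FAS), two-sided at 0.05, and names the method: "Paired t-tests will be performed to determine the significance of differences". Neither 2.8.3 nor 2.8.4 mentions period or sequence.

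Besides ineligible patients, the FAS in 2.8.2 leaves out "cases that have never received any study treatment after randomization, and cases with no measurements made after randomization". A patient treated and measured on one day only therefore stays in it.

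**The concern.** A paired t-test pools the within-patient treatment differences of both groups as a single sample. In a two-period crossover, any systematic difference between the periods in the analysed quantity then appears as scatter between patients, although the randomised order would allow it to be removed.

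Such a difference is plausible here. Day 1 compares a first exposure to heat with a second, and Day 2 compares a third with a fourth; habituation or sensitisation need not be the same across the two pairs. Expectation may differ between a first and a second injection, and the Discussion itself raises a placebo effect on this pain.

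At stake is mainly a missed effect in a rare condition where ten patients are all the trial plans to have. If the two orders contribute unequal numbers, the estimate also picks up part of the period difference.

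**Working it through.** **Inputs from the protocol article.** 5 + 5 patients (2.8.1); two-sided 0.05 and a paired t-test (2.8.3); endpoint is the change from a same-day pre-dose load (2.6.1, 2.6.2, 2.7.1). The sample size rests on feasibility, so there is no stated power, effect or SD to reproduce.

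**Assumptions.** SD of the icatibant-minus-placebo difference within a sequence: 20 mm. True effect: 20 mm. D from 0 to 20 mm. The document gives none of these; only their ratios matter for power.

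**Step 1: which shifts matter.** For each patient, d = (icatibant post − pre) − (placebo post − pre). A shift that moves both loads of Day 2 equally drops out of post − pre. Simulated with Day 2 pain 20 mm lower at both loads (load-level residual SD 10 mm, no scale limits), the SD of d stays at 20.0 mm and the bias is 0. A 20 mm shift in the Day 2 change itself raises the SD of d to 29.1 mm.

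**Step 2: algebra.** Let D be the Day 2 minus Day 1 difference in the change and τ the treatment effect.
- Group A (icatibant on Day 1): E[d] = τ − D
- Group B (icatibant on Day 2): E[d] = τ + D
- Bias of the pooled mean = D(nB − nA)/N
- Expected sample variance of d at 5/5 = SD² + (10/9)D²

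For D = 10: 400 + 111.1 = 511.1, SD 22.6 mm (+13%). For D = 20: 400 + 444.4 = 844.4, SD 29.1 mm (+45%). For D = 5: 400 + 27.8 = 427.8, SD 20.7 mm (+3%).

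**Step 3: test behaviour at 5/5 (simulation).** The adjusted test averages the two sequence means of d and uses the pooled within-sequence SD with N − 2 = 8 df (critical t 2.306, against 2.262 on 9 df).

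| D (mm) | Power, paired t | Power, adjusted | Type I error, paired t |
|---|---|---|---|
| 0 | 80% | 79% | 5.0% |
| 5 | 78% | 79% | 4.4% |
| 10 | 72% | 79% | 3.0% |
| 15 | 62% | 79% | 1.6% |
| 20 | 48% | 79% | 0.7% |

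The adjusted test stays at about 5% type I error throughout.

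**Step 4: unequal sequences.** In absolute size:
- 5/4: D × 1/9, so 1.1 mm at D = 10 and 2.2 mm at D = 20
- 5/3: D × 2/8 = D/4, so 2.5 mm and 5 mm
- 4/4: zero

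The sign depends on which group loses patients and on the direction of D. The adjusted estimate has no such bias.

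**Step 5: price of adjusting when D = 0 (noncentral t).**
- 5/5: 80.3% to 79.1%, about 1 point
- 5/4: 74.8% to 72.5%, about 2 points
- 5/3: 68.1% to 63.0%, about 5 points

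**The case against.** The strongest reply is that the design already protects the endpoint. Each day has its own pre-dose load, so the ordinary day-to-day drift in pain that worries one in a crossover is subtracted out. This stands, and it rules out a tempting broader reading, that any Day 1 to Day 2 shift in heat-induced pain contaminates the test. It does not, apart from scale limits. Those limits are a real qualification. The Introduction describes pain reaching 100 mm, and 2.6.1 stops a load when pain is unbearable, so near the ceiling a level shift may not cancel fully.

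Second, the large losses need a D of half to all of the assumed effect, and nothing in the document supports that size for a within-day change. At D = 5 mm the two tests are nearly equal, and with no period difference the paired test is slightly better. This also stands; the table is a range, not a forecast.

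Third, a reader might infer that the planned test risks a false positive. At 5/5 it does not: type I error is at or below 5%. In the simulations it rose visibly above 5% only at 7/3 (up to 6.3%), a split that exclusions from 5/5 cannot produce. Attrition should also be low over three inpatient days, and two losses unbalance the groups only if both fall in the same one.

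Fourth, the trial is exploratory and claims no power. That lowers the severity. It does not make the less efficient test preferable, because 2.8.3 still sets a significance threshold. Nor is the method left to an unseen analysis plan: the article names the test.

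**Conclusion.** The point holds in a limited form. The named primary test ignores the treatment order by which the trial randomises, so a Day 1 to Day 2 difference in the before-to-after VAS change is counted as error. In the planned 5/5 design this costs power only: from 80% to 72% at D = 10 mm and to 48% at D = 20 mm, assuming an SD and an effect of 20 mm each. Bias arises only with unequal analysed sequences and is small after one loss.

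The document does not support saying that the primary result would be invalid or anti-conservative. Whether D is material is unknown. Severity: a recommended, cheap improvement rather than a mandatory correction.

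**What to change.** In 2.8.3, make the primary analysis period-adjusted, by either of two routes:
- a linear mixed model with treatment and period as fixed effects and patient as random effect; or
- the Hills-Armitage comparison, a two-sample t-test of within-patient Day 1 minus Day 2 differences between Groups A and B.

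The mixed model can also use a FAS patient with only one treated day. The Hills-Armitage comparison cannot: like the paired t-test, it needs both days. Keep the paired t-test as a sensitivity analysis, and settle the choice before unblinded data are seen.

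The change is to wording only. If there is no period effect, it gives up about 1 power point at 5/5, 2 at 5/4 and 5 at 5/3.

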#### 2.8.4. Analysis of the secondary endpoints.

The FAS will be the population to be analyzed. A comparison of the change in duration of dermal pain induced by thermal load will be examined at a significance of *P* < .05 between the icatibant and placebo treatment phases. Additionally, changes of blood and plasma histamine levels and serum ACE levels before and after treatment will be analyzed at a significance of *P* < .05 between both treatment phases. A secondary analysis will be performed using the PPS as the analysis population by the same statistical methods. Skin samples will be collected for the histological evaluation of dermal pain. In some patients, a prior skin biopsy may have been performed at the site of dermal pain in conditions consistent with those in this study. The previous specimens will be evaluated in those cases.

#### 2.8.5. Safety assessments.

In the population of study subjects who receive at least 1 study treatment, the number and incidence of adverse events and the number of subjects suffering from adverse events will be investigated in each phase of the icatibant and placebo treatment.

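### The safety analysis omits anyone heated but never injected, and gives adverse events at the pre-drug heat loads no category of their own

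*Protocol article*

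**What the plan says.** Section 2.8.5 (Safety assessments) fixes two things. The population is stated, together with what is counted in it: "In the population of study subjects who receive at least 1 study treatment, the number and incidence of adverse events". The tabulation is also stated: adverse events "will be investigated in each phase of the icatibant and placebo treatment". No third category is given.

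Section 2.7.3 (Adverse events) says what the safety evaluation is meant to cover: "Safety concerns in this study are assumed to be associated with the administration of icatibant and the induction of dermal pain by thermal stimuli". Section 2.10 (Harms) defines an adverse event by its suspected link to the conduct of the study, not to the drug, so a harm from heating qualifies.

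The schedule puts heating before drug on both days. Allocation comes first (section 2.2): "Upon enrollment, participants will be assigned to 1 of 2 groups". On Day 1 the drug "will be subcutaneously injected at least 90 minutes after the first thermal load", or later if skin symptoms take longer to settle. Section 2.6.1 also foresees a badly tolerated load: "If unbearable dermal pain occurs during heating, the thermal load will be discontinued". Day 2 repeats the sequence, with "the (3rd and 4th) thermal load before and after drug administration".

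**The concern.** A safety set of treated patients is the usual convention, and it works when exposure to risk begins with the drug. Here it begins earlier. A study procedure that the protocol itself lists as a safety concern is carried out on randomised patients before any injection, and again before the second one.

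Two gaps follow. The population rule shuts out a patient who is heated, harmed and never injected. The two-cell tabulation has nowhere to report harm from a pre-drug load as what it is. At stake is whether the final report can describe one of its two stated safety concerns separately, and whether the icatibant and placebo event rates can be read as post-drug rates.

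**Working it through.** The article gives no adverse event rate, safety margin or safety power, and section 2.8.1 justifies ten patients by rarity and feasibility. There is no figure to reproduce. The check is a count from the schedule, followed by illustrations with assumed rates.

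**Count of loads (sections 2.6.1, 2.6.2 and 2.8.1).**
- Day 1: load 1 before the drug, load 2 after it. Day 2: load 3 before, load 4 after.
- Per patient: 2 of 4 loads are pre-drug. In ten patients: 10 × 4 = 40 loads, of which 10 × 2 = 20 are pre-drug.

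**Who is in the safety population.** Allocation precedes load 1, and load 1 precedes the first injection by at least 90 minutes. A patient who leaves in that interval has received no study treatment and is outside the population in 2.8.5, however a phase is defined. The full analysis set in 2.8.2 also excludes patients never treated, so no defined analysis set holds this patient. With assumed probability p that a given patient leaves at load 1, the chance that at least one of ten is missing is 1 − (1 − p)^10:

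| p (assumed) | chance that at least one of 10 is missing |
|---|---|
| 2% | 18% |
| 5% | 40% |
| 10% | 65% |
| 20% | 89% |

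One such patient is 1/10 = 10% of those heated.

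**Where pre-drug events go in patients who continue.** The article does not say when a phase starts and ends.
- Phase = treatment day. Section 2.8.4 points this way, because it compares before-to-after changes between treatment phases, and both measurements are taken on the same day. Events at loads 1 and 3 are then counted under a drug not yet given that day.
- Phase = injection to next injection. Load 1 events then have no phase, and load 3 events fall under the Day 1 drug.

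Neither reading provides a separate line for pre-drug events.

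**Effect under the treatment-day reading.** Let h be the assumed probability of an adverse event per load, independent between loads, with no drug effect. The incidence per phase is 1 − (1 − h)², against h for the post-drug load alone:

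| h (assumed) | post-drug load only | whole-day phase |
|---|---|---|
| 5% | 5% | 9.8% |
| 10% | 10% | 19% |
| 20% | 20% | 36% |
| 30% | 30% | 51% |

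Both phases rise by the same amount, because each contains one pre-drug load. Now let icatibant alone cause an event with assumed probability q = 20%. The icatibant-minus-placebo difference is q(1 − h) for the post-drug load and q(1 − h)² for the whole day:
- h = 10%: 0.2 × 0.9 = 18 points, against 0.2 × 0.81 = 16.2 points.
- h = 30%: 0.2 × 0.7 = 14 points, against 0.2 × 0.49 = 9.8 points.

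**The case against.** The strongest reply is that a treated-patients safety set is standard, that a condensed article may leave phase boundaries to the full protocol or analysis plan, and that no harm goes unobserved: sections 2.7.3 and 2.10 require monitoring and management of any study-related event. All three statements are correct. They limit the point to analysis and reporting, and they mean that the undefined phase boundary is not itself a fault. They do not remove the point. The population rule is stated in 2.8.5, not left open, and a wider set elsewhere would contradict it. The two-way tabulation is stated too.

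A reader might go further and infer that the Day 1 drug is charged with two loads (2 and 3) and the Day 2 drug with one (4), giving a two-fold difference by order. That needs the injection-to-injection reading, which the article does not adopt and which the usage in 2.8.4 speaks against. With the treatment day as the phase, each drug has two loads. Even on the other reading, the imbalance cancels between drugs at the planned 5:5 allocation.

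A reader might also infer that the patients worst affected by heating are the ones most likely to be left out. The article does not say so. Section 2.6.1 stops the load for unbearable pain and continues with examinations and blood sampling, and it times the injection to wait for symptoms to resolve. Stopping a load is not described as withdrawal.

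**Conclusion.** The point holds in two parts. First, a randomised patient harmed at load 1 who is never injected is left out of the safety analysis. This assumes only that study treatment in 2.8.5 means an injection of icatibant or placebo, which the rest of that sentence supports. Second, events at half of the heat loads (20 of 40) have no category of their own, so provocation harm cannot be reported separately although section 2.7.3 names it as a concern.

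The direction of the second effect depends on the phase definition. On the likelier treatment-day reading it is inflation of both phases and dilution of the contrast. The documents do not support a claim that one drug is systematically charged with the other's events. All percentages above rest on assumed rates and show the range only. Severity is minor to moderate: the trial is exploratory with ten patients, the events are still monitored, and what suffers is the summary.

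**What to change.** In section 2.8.5:
- Define the safety population as all randomised patients who start the first thermal load.
- Report adverse events in three categories: pre-drug load (loads 1 and 3, before that day's injection, with all heated patients as the denominator), after icatibant, and after placebo.
- List load 3 events with the Day 1 drug noted, so that a late effect of that drug can still be considered.

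The cost is a change of wording and one extra table column. No trial procedure changes. The new categories need event onset relative to injection on record. The article does not state that it is recorded, so this is an assumption to confirm. The reported number of adverse events may rise.
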